### Measures

The following primary outcome measures will be completed as self-report scales by parents/caregivers (both mothers and fathers) at pre-intervention, post-intervention and three-month follow-up assessment to evaluate the effectiveness of the online parenting program:
*Strengths and Difficulties Questionnaire* (SDQ; [41]) will measure child emotional/behavioural adjustment. The total difficulties score will be used to measure child emotional and/or behavioural problems; the conduct problems and hyperactivity subscales will be used specifically to measure externalising behaviour problems.
*Parent Problem Checklist* (PPC; [42]) problem score will measure disagreements between parents over childrearing issues in two-parent families only.Two subscales from the *Parenting and Family Adjustment Scales* (PAFAS; [43]) will be used to measure both dysfunctional and positive parenting.

For completion of the SDQ, caregivers with more than one child will be asked to select a ‘target’ child to answer these questions about. The target child is the child aged 2–16 whose behaviour or development the parent/caregiver is most concerned about, or, if they have no concerns about their children, the youngest child within this age range. The first caregiver to register for the program will select this target child, and to ensure both caregivers are answering questions about the same child, the child’s name will then be used in the questionnaires completed by the second caregiver (however, this name will not be included in the study dataset).

The K6 [44] will be used as a secondary outcome measure to measure parental mental health at pre-intervention, post-intervention and follow-up assessment.

At pre-intervention, all participating parents will complete a range of socio-demographic questions about themselves and their families, and information about the target child (such as age, diagnosis of mental health problems, and previous assistance for child’s emotions, behaviour or development). Further questions were developed specifically for the study to assess: amount of time co-parents spent discussing program content (at post-intervention only); level of perceived involvement of parent in child’s life (pre-intervention only); level of chaos in home environment (pre- and post-intervention); and whether any additional assistance had been sought since commencing the program (post-intervention only). Satisfaction with the program will be assessed at post-intervention with five items from Eyberg’s *Therapy Attitude Inventory* [45].

Participating caregivers will be asked a range of questions which are built into each video module. If two caregivers are registered for the program, they will first be asked to select who is watching the module and subsequent questions will then be directed only to those caregivers who are viewing the module (although names will not be included in the study dataset). At the start of each module, caregivers will be asked to rate their child’s behaviour (on a 10-point scale from ‘no behaviour problems’ to ‘significant problems’) and their parenting confidence over the previous week (on a 10-point scale from ‘not at all confident’ to ‘extremely confident’). From module 3 onwards, they will also be asked the extent to which they used the strategies from the previous module, on a 10-point scale from ‘not at all’ through to ‘frequently’. At the end of each module, caregivers will rate the module content on a 7-point scale from ‘not at all helpful’ through to ‘extremely helpful’.

### Data collection procedure

Information from participating parents/caregivers will be collected through online questionnaires completed at three time points (as detailed above) with email reminders sent up to three times to ensure high rates of questionnaire completion. Weekly data about parent confidence, child behaviour and use of program strategies will also be collected, as well as number of times each module is viewed. No identifying information will be included in the dataset. Data will be periodically downloaded to the University of Sydney server and stored on a password-protected computer drive accessible only to project staff based at the University.

### Data analysis procedure

Analyses of changes from pre- to post-intervention and at three-month follow-up on the primary and secondary outcome measures for mothers and fathers will be conducted using repeated measures univariate and multivariate analyses. Propensity score matching will be used to examine the overall intervention effects accounting for the bias of family structure (e.g., father involvement in two-parent families). To examine the effect of level of father involvement in the program (in two-parent families) on child outcomes (as rated by mothers), regression-based analyses will be used. Similarly, regression-based analyses will also be used to examine the predictors of father engagement and the moderators and mediators of the intervention effects. Data will be analysed using SPSS Statistics 22 and M*plus*. The plan for the management of missing data will be informed by missing data analyses used to determine whether data is missing at random or not. If the analysis indicates the missing data is not random, or missing data is extensive, multiple imputation procedures will be used.

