### Objective

This paper describes the protocol for a quasi-experimental repeated measures study that examines the effectiveness of a universal, online parenting intervention called ParentWorks, in reducing father- and mother-reported child externalising behaviour, dysfunctional parenting and parental conflict, and increasing positive parenting. The key research questions include:Does participation in the online parenting program significantly reduce father- and mother- reported dysfunctional parenting, parenting conflict and child externalising behaviour and increase positive parenting from pre- to post-intervention, and are these changes maintained at three-month follow-up?Does participation of fathers (in two-parent families) enhance the outcomes of the intervention in terms of reductions in mother-reported child behaviour problems?What variables predict father engagement in the online parenting program (including socio-demographic variables such as father age and education, and family variables such as parenting conflict and relationship satisfaction)?What are the moderators and mediators of the effectiveness of the online parenting program?

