## Methods/Design

### Design

This study is an uncontrolled, single group clinical trial, involving a quasi-experimental, repeated measures design with three assessments (pre-intervention, post-intervention and three-month follow-up). After reading and signing an online consent form, participating parents will complete a pre-intervention questionnaire. Participants will complete the program at their own pace, and then complete a post-intervention questionnaire. Three months after completing the post-intervention questionnaire, they will complete a follow-up questionnaire. The study has been approved by the University of Sydney Human Research Ethics Committee (Project No. 2016/452) and is registered with the Australian New Zealand Clinical Trials Registry (ACTRN12616001223426).

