### Sample size

The sample size calculation was conducted with G*Power [46]. To detect a small effect of ParentWorks on the primary measure of child outcomes (SDQ; Goodman, 2007) with *d* = 0.2 and 0.8 power, a final sample size of 800 two-parent families is required. Of these families, we expect that approximately 400 fathers will elect to participate. In order to account for attrition rates, and participation of single-parent families, we aim to recruit at least 1200 families. This sample size will also be sufficient to conduct the analyses examining level of father involvement, predictors, moderators, and mediators. There are no plans to carry out interim analyses.

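### With no untreated group, moderators and mediators cannot be identified as effects of the programme, and the blanket statement that the sample suffices for them is unsupported

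*Protocol article*

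**What the plan says.** The Design section of the protocol article states: "This study is an uncontrolled, single group clinical trial, involving a quasi-experimental, repeated measures design with three assessments". The fourth research question, under Objective, asks "What are the moderators and mediators of the effectiveness of the online parenting program". The Data analysis procedure section answers it with one clause: "regression-based analyses will also be used to examine the predictors of father engagement and the moderators and mediators of the intervention effects".

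The Sample size section reports one calculation, for the SDQ: "with *d* = 0.2 and 0.8 power, a final sample size of 800 two-parent families is required". It adds that "we expect that approximately 400 fathers will elect to participate" and that "In order to account for attrition rates, and participation of single-parent families, we aim to recruit at least 1200 families". It then asserts: "This sample size will also be sufficient to conduct the analyses examining level of father involvement, predictors, moderators, and mediators". No effect size, covariate prevalence, path size or power is given for any of those further analyses.

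The Discussion concedes that a single-group design cannot control confounding such as maturation, and that this limits what can be concluded about effectiveness. It does not link that limitation to the moderator and mediator aims, which keep their wording.

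**The concern.** A moderator of an intervention effect is a variable across which the treated-versus-untreated difference varies. A mediator is a variable that carries part of that difference. Both need a contrast between receiving and not receiving the programme, and this design has none. A regression of change on a covariate estimates the sum of two things: how programme benefit varies with the covariate, and how change without the programme varies with it. The data cannot split the sum.

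The second part is unlikely to be negligible here. Under Measures, a parent with several children rates the child who worries them most, which invites regression to the mean. The age range of 2 to 16 years leaves room for natural change that differs by age. Parenting and child behaviour are both parent-reported at the same three assessments, so their changes may move together without one causing the other.

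The article hopes to inform public policy. A statement that the programme works better for certain families, or works through a certain parenting change, would be read causally. Readers would also take the sufficiency sentence as assurance that a null moderator result is informative.

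**Working it through.** **Inputs from the article:** single group, all treated; d = 0.2; power 0.8; 800 two-parent families; about 400 participating fathers.

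**Assumptions, because the article gives no values:** two-sided alpha 0.05; pre-post correlation r = 0.7; the covariate correlations, splits and path sizes shown below.

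**1. Reproducing 800.** For two independent groups, n per group = 2 × (1.96 + 0.84)² / 0.2², which is 393 with unrounded quantiles, or 786 in total (788 with the exact t-test). Power at 400 v 400: 0.2 / √(2/400) = 2.83; 2.83 − 1.96 = 0.87; power 0.81. A one-sided two-group test gives 620. A paired pre-post test at d = 0.2 needs only 199. So 800 fits a two-group comparison, apparently families with and without a participating father, and that comparison has little reserve.

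**2. Identification.** Write change = a + bT + cM + d(T × M), where T is programme receipt and M a covariate. With T = 1 for everyone, the four columns [1, T, M, T × M] have rank 2. Only a + b and c + d can be estimated. The moderation term d is never separate from c, the covariate's relation to natural change.

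**3. Illustration of regression to the mean.** Assume no programme effect, an unadjusted change score, and a covariate related to the post score only through baseline. With ρ the covariate's correlation with baseline, the slope in baseline SD units has size ρ(1 − r), and SE = √(2(1 − r) − slope²) / √800.

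| ρ | slope | SE | z | flagged at 0.05 |
|---|---|---|---|---|
| 0.1 | 0.03 | 0.027 | 1.1 | about 20% |
| 0.3 | 0.09 | 0.027 | 3.3 | 91% |
| 0.5 | 0.15 | 0.027 | 5.6 | >99% |

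Under this model, adjusting for baseline brings the slope to zero. It does not remove natural course. In 2,000 simulated trials of 800 with no programme effect, a covariate tied to natural change at 0.1 SD per SD was flagged in 80%.

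**4. What 800 can support.**

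- Binary predictor of change, difference 0.2 (SD of the analysed score = 1), share s: SE = √(1/(Ns) + 1/(N(1 − s))). Power at 800 is 0.81 at 50/50, 0.74 at 30/70, 0.62 at 20/80 and 0.40 at 10/90. Among 400 fathers it is 0.52 at 50/50.
- Mediation, joint significance of two equal standardised paths (Fisher z). At N = 800, paths of 0.10 give 0.65 and paths of 0.14 give 0.96. At N = 400 these fall to 0.27 and 0.64.
- Father participation × balanced binary covariate, 200 families per cell: SE = √(4/200) = 0.141. Detectable size = 2.80 × 0.141 = 0.40 SD. An interaction of 0.2 has 0.29 power and needs 16 × 2.80² / 0.04, about 3,140 families.
- The same interaction with baseline adjustment at r = 0.7: residual SD = √(1 − 0.49) = 0.714. Detectable size = 0.714 × 0.396 = 0.28 SD. An interaction of 0.2 needs 0.51 × 3,140, about 1,600 families. At 800, z = 0.2 / (0.714 × 0.141) = 1.98, so power is about 0.51.

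**The case against.** The strongest reply is that the root limitation is disclosed. The Discussion names uncontrolled confounding and promises tempered conclusions, and reporting will follow a guideline for non-randomised designs. On that view only terminology is left. The disclosure is real, but it is general: research question 4 and the analysis clause still promise moderators and mediators of an effect that the design cannot isolate.

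Several further points on that side stand and limit the concern:

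- A reader might infer that nothing can be estimated. That goes too far. Associations with change can be estimated. Father participation varies between families, so a contrast involving it is estimable, though not randomised and open to confounding.
- A reader might infer that every variable related to baseline severity will look like a moderator. At a correlation of 0.1 it is flagged in only about 20% of trials under the stated model.
- The figure above 99% does not describe a planned analysis. The article says only that regression will be used. Whether baseline is adjusted for may be set in a fuller plan.
- The article does not say that mediation will rest on concurrent change reported by one parent. Three assessments, reports from both parents, in-module ratings and Mplus allow time-ordered or cross-informant models. These improve the evidence but do not supply the missing untreated contrast.
- A reader might infer that the sufficiency sentence is false. It is unsupported rather than wrong throughout: some of the analyses it covers are adequately powered at 800. The article also does not specify the father-participation interaction used above as the hardest case.

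**Conclusion.** The point holds in two parts. First, in this design, moderators and mediators cannot be identified as effects of the programme. This follows from the design alone and needs no numerical assumption. The percentages of 20%, 91% and above 99% are illustrations. They depend on no programme effect, r = 0.7, N = 800, no baseline adjustment, and a covariate linked to the post score only through baseline.

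Second, the sufficiency statement has no stated support. With two-sided 0.05 assumed, 800 may be enough for a balanced binary predictor at 0.2 or for mediation paths of about 0.14 or more. It is not enough for a father-participation interaction of 0.2, where balanced power is 0.29 unadjusted and about 0.51 with baseline adjustment at r = 0.7. Unbalanced covariates and analyses confined to the 400 fathers also fall short at 0.2.

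The documents do not support the broader readings that these analyses are impossible or that the sample is inadequate for all of them.

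**What to change.** - Restate research question 4 and the matching analysis clause as predictors and correlates of change. Adjust for the baseline value of the outcome and report the results as associations.
- Keep the word moderator only for father participation × covariate, described as a non-randomised contrast.
- For mediation, use the time ordering that the assessments already provide and report associations. No single model needs to be fixed here.
- Replace the sufficiency sentence with the detectable effect for each analysis and its assumptions (alpha, covariate split, pre-post correlation, whether baseline is adjusted for), or limit it to the analyses it supports.

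No new data are needed. The cost is rewording, a modest change to the regressions, and weaker claims about for whom and how the programme works.

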### Sample size

The sample size calculation was conducted with G*Power [46]. To detect a small effect of ParentWorks on the primary measure of child outcomes (SDQ; Goodman, 2007) with *d* = 0.2 and 0.8 power, a final sample size of 800 two-parent families is required. Of these families, we expect that approximately 400 fathers will elect to participate. In order to account for attrition rates, and participation of single-parent families, we aim to recruit at least 1200 families. This sample size will also be sufficient to conduct the analyses examining level of father involvement, predictors, moderators, and mediators. There are no plans to carry out interim analyses.

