Parenting interventions generally target both mothers and fathers (the core parenting team), but father participation rates are often very low, or not reported at all [11]. Importantly, there is evidence that including fathers in traditional face-to-face parenting interventions leads to improved outcomes. Lundahl et al. [12] conducted a meta-analytic review (*k* = 26) and found that father engagement in parenting interventions was associated with reduced child externalising behaviour and improved parenting behaviour in the short-term, but not in the longer-term. However, other research has found long-term improvements in child outcomes when fathers are included in interventions [27, 28]. Although there are likely to be many reasons for the low rates of father participation, there has been very little research to date about fathers’ perceptions regarding barriers and facilitators to participation [29]. However, three surveys with fathers have found that cost of the service, lack of time and work commitments consistently emerge as key barriers to participation [29–31].

Providing parenting interventions online has the potential to address many of the practical barriers that may prevent fathers from participating in traditional face-to-face interventions. Indeed, there is evidence that fathers prefer online interventions over face-to-face formats [29, 31]. However, like face-to-face interventions, rates of father participation in online parenting interventions are often not reported. Of the 12 papers included in the meta-analysis of online parenting interventions [10], 11 either reported mother results only or did not provide a breakdown of parent gender. This suggests that researchers continue to disregard the importance of both reporting on parent gender and including mothers and fathers in parenting interventions [11]. Consequently, the rates of father engagement in online parenting interventions are unknown. Researchers have highlighted that parenting programs have been designed and tested with mothers, and it may be critical to provide a program that meets the needs and preferences of fathers, in order to achieve high rates of father engagement [32–34].

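### The 800-family requirement is stated for the effect of ParentWorks, but it matches a two-independent-group comparison; the single-group pre-post change needs about 199 raters

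*Protocol article*

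**What the plan says.** The Design section states: "This study is an uncontrolled, single group clinical trial". There are three assessments and no control. The Data analysis procedure section examines change over time by repeated-measures methods, separately for mothers and fathers. It assigns regression to the effect of the level of father involvement on mother-rated child outcomes.

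The Sample size section gives the purpose of the calculation as "To detect a small effect of ParentWorks on the primary measure of child outcomes", the SDQ, "with *d* = 0.2 and 0.8 power", and concludes that "a final sample size of 800 two-parent families is required". It continues: "Of these families, we expect that approximately 400 fathers will elect to participate". The recruitment target of 1200 families allows for attrition and single-parent families. The section then says that the sample will be large enough for the analyses of father involvement, predictors, moderators and mediators as well. On method it says "The sample size calculation was conducted with G*Power", without the test family, alpha, sidedness or a pre-post correlation.

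**The concern.** Without a control group, the effect of ParentWorks on the SDQ can only be a change within the same rater. Such a change is tested on paired differences and needs far fewer raters than a comparison of separate groups at the same d. A requirement of 800 therefore looks as if it belongs to another comparison. Two details point the same way: the number is counted in two-parent families, and half of the fathers are expected to take part.

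If so, the stated power of 0.8 describes neither question properly. For the pre-post question (the first research question) it is too low, and readers will not realise that very small changes can be detected. For the father-participation question (the second research question), 0.8 is close to the best case, yet the text offers only a general assurance that the sample suffices.

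**Working it through.** **Inputs.** From the Sample size section: d = 0.2, power 0.80, 800 two-parent families, about 400 participating fathers. Assumed: alpha 0.05 two-sided, because neither is stated. The section also says "There are no plans to carry out interim analyses", so no interim look splits alpha. The normal quantiles sum to 1.960 + 0.8416 = 2.8016. The sample sizes and powers called exact use the noncentral t.

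**1. Reproducing 800.** Two independent groups, 1:1:

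n per group = 2 × (2.8016 / 0.2)² = 392.4, so 393 (786 in total). The exact t test gives 394 per group, 788 in total. With 400 per group the power is 0.806. This is within 2% of 800.

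Variants that do not give 800:
- two groups, one-sided: 620; two groups, power 0.9: 1054
- paired, dz = 0.2: 199 two-sided, 156 one-sided, 265 at power 0.9
- paired, alpha 0.01 or 0.001: 296 or 433
- repeated-measures ANOVA with f = 0.1, two or three assessments, correlation 0 to 0.7: 98 to 395 for the within-subject or interaction effect, 264 to 670 for the between-group effect

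**2. The question as worded (one-group change).** If d is the standardised mean change (dz):

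n = (2.8016 / 0.2)² = 196.2; the exact t test gives 199.

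If d is on the raw SDQ standard deviation, dz = 0.2 / √(2(1 − r)), with r the assumed pre-post correlation:

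| r | dz | n needed | power with 800 |
|---|---|---|---|
| 0 | 0.141 | 395 | 0.979 |
| 0.3 | 0.169 | 277 | 0.998 |
| 0.5 | 0.200 | 199 | >0.999 |
| 0.7 | 0.258 | 120 | >0.999 |
| 0.8 | 0.316 | 81 | >0.999 |

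The change detectable with 80% power is dz ≈ 2.8016 / √800 = 0.099 for 800 mothers and 2.8016 / √400 = 0.140 for 400 fathers. With 400 fathers the power at dz = 0.2 is 0.979.

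**3. The father contrast.** Unadjusted two-group t test, 800 families, d = 0.2, noncentrality 0.2 × √(n₁n₂/800):

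| Father participation | n₁ / n₂ | noncentrality | power |
|---|---|---|---|
| 50% | 400 / 400 | 2.83 | 0.81 |
| 40% | 320 / 480 | 2.77 | 0.79 |
| 30% | 240 / 560 | 2.59 | 0.74 |
| 20% | 160 / 640 | 2.26 | 0.62 |

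Two things move these figures:
- **Baseline adjustment raises them, if d is on the raw SDQ scale.** The effective d becomes 0.2 / √(1 − r²). For assumed r of 0.5 or 0.7, power is 0.85 or 0.95 at 30% participation and 0.74 or 0.89 at 20%. If d is already on the change scale, the table stands.
- **Missing mother ratings lower them.** As an illustration, if 640 of 800 families (80%, assumed) had mother-rated data, split evenly, the noncentrality is 0.2 × √160 = 2.53 and the power 0.71.

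**The case against.** The strongest reply is that the error is conservative for the headline question. At 5%, 800 exceeds the need under every pre-post variant tried, so no recruitment, data collection or analysis has to change. That stands, and it limits the weight of the point.

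The origin of 800 is also an inference. The test family and alpha are not printed, and a condensed article may leave them to the full protocol. Another route exists: a paired test with d on the raw scale and zero correlation needs 395, close to the 400 expected fathers, and 50% uptake then leads to 800 families. Zero correlation between repeated SDQ scores is implausible, so the father contrast remains the likelier source, but it is not a stated fact. The mismatch does not depend on it: the article prints an N, a d, a power and a target effect that do not agree for a one-group change.

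A reader might go further in three ways that the document does not support:
- **That power for the father question needs an exact 50:50 split, or that the 50% is concealed.** Power is still 0.79 at 40%, and the expected 400 fathers are printed. The Background remark that "father participation rates are often very low, or not reported at all" concerns parenting interventions in general. The same section says that rates for online programmes are unknown, that fathers prefer online formats, and that a father-adapted programme achieved high participation. The 50% has no supporting figure, but the document does not contradict it.
- **That propensity matching will erode power for the father question.** The Data analysis procedure section assigns matching to the overall intervention effects, and regression to the mother-rated father question.
- **That significance at 5% is the wrong success rule for the pre-post question.** The article sets no such rule, so there is nothing to correct.

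**Conclusion.** The statement is wrong as written and should be corrected. On an assumed two-sided 5% test, the single-group effect at d = 0.2 needs about 199 raters (81 to 395 over assumed correlations of 0.8 to 0), and 800 raters give power of at least 0.98. The printed 800 and 0.8 belong to a two-independent-group comparison, most likely father participation versus none.

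A reader might infer that the trial is underpowered for its main question; the opposite is true. The father contrast has almost no margin above 0.8 in an unadjusted analysis, and power falls materially from about 30% participation downwards. Those figures describe one scenario: the planned analysis is a regression on level of involvement, whose power depends on the scale of d, on adjustment and on complete mother ratings. The unqualified assurance about the father analyses is therefore unsupported, not shown to be false.

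**What to change.** Rewrite the Sample size paragraph in three respects.

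1. The sponsor names the test, alpha, sidedness, comparison and meaning of d (raw SDQ scale or change scale) behind 800. If it was the contrast by father participation, say so and attach the number to the second research question.
2. Add a separate pre-post figure: about 199 raters per informant for dz = 0.2, with 800 mothers or 400 fathers detecting dz of about 0.10 or 0.14 at 80% power.
3. Replace the general assurance with power for the father question at several participation rates (for example 50%, 40%, 30% and 20%), stating whether baseline is adjusted for and how many families are expected to have mother-rated data. The calculation should match the planned regression on level of involvement as far as possible.

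The cost is one reworded paragraph and a less favourable stated power for the father question. No extra recruitment and no change to data collection is needed.
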